**Sample size estimation:**

1. **Sample size estimation in a between subjects 2x2 factorial design (Bonnet,2016)**

**
[figure not shown]
**

In order to estimate a main effect in a between-subjects 2x2 factorial design at 95% confidence, at desired confidence interval width of 2.0, and a planning value of 8.0 for the average within group error variance, the contrast coefficients are 0.5, 0.5,-0.5 and-0.5, and the sample size required per group is approximately 31.

1. **Sample size estimation using two proportions:**

The PD program has been reported to increase weight of ≥200g in 12 days among 87% of participants in Burundi [^10^](#_ENREF_10). Based on the prevalence of malnutrition (<-2sd in any of HAZ,WAZ,BMIZ) among the CURIE CP population based cohort reported as 64% as per the 2015 assessments. Assuming the previously reported effect of the PD program, we hope to reduce malnutrition in the CP child population to about 29%, at α =0.05, and power (1-β) =0.8. After imputing these parameters into a Stata program to estimate sample size for individual randomization, of a two proportions test, the estimated total sample size is 62: Hence 31 participants per each of the four arms. Therefore for a 2x2 factorial trial, assuming a 1:1:1:1 allocation, 124 participants will be required for the study with 32 participants in each of the four conditions.

Participants in this study will include eligible caregivers of children with CP participating in the wider CURIE intervention study (Akwenda). In order to account for those that may not be malnourished from the CURIE study sample, additional caregivers of malnourished children with CP will be recruited from community-based organizations (CBOs) operating within the study setting including EKISA ministries and MUSANA community health centre. The CURIE intervention study has got two arms (PFT and Control) separated as village clusters based on geographical proximity and balanced by age, and GMFCS level. This study will utilize the available CURIE intervention clusters to avoid contamination. Details of participant recruitment from different CBOs are displayed below.

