**Defining malnutrition**:

Anthropometric indicators will be constructed according to WHO growth standards based on weight, height/length, age and sex[^11^](#_ENREF_11) and converted into Z-scores using the WHO Anthro[^13^](#_ENREF_13) and Anthro-Plus to calculate the nutritional status for children within the 2-19 years age range. For those older than 19 years, the LMS method will be used to determine their weight, height and body mass index (BMI) by age and sex standard deviation scores[^14^](#_ENREF_14). Children with a Z-score of < -2 SD in any of the nutritional indicators will be defined as having Malnutrition. Classifications for MUAC will be made by comparing the arithmetic mean of the two measurements (i.e. the “gold standard” measurement) against case defining thresholds for moderate acute malnutrition (MAM) i.e. for children, MUAC < 12.5 cm and severe acute malnutrition (SAM) MUAC < 11.5cm[^15^](#_ENREF_15)^,^ [^16^](#_ENREF_16). For adult (>18years) thresholds, MAM MUAC <23.0 cm and SAM MUAC <21.0cm[^17^](#_ENREF_17). The caregiver of a child or adolescent who is identified as MAM will be enrolled for the intervention study consecutively to make-up for the required study sample (124 caregivers). Caregivers of children or adolescents identified as serious SAM will be counselled about the life saving importance of early management of malnutrition and thereafter referred to the nearest treatment site based on ministry of health guidelines [^18^](#_ENREF_18). Anthropometric findings for those enrolled will be recorded as baseline for the intervention study.

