**Outcome measures**

**Primary outcome**: Nutritional status: The primary outcome measure will be a weight gain of >200grams in 12 days[^10^](#_ENREF_10) and ≥ 900g within 3 months.

**Secondary outcomes** will include change in anthropometric Z scores for any of weight, height and BMI, and MUAC classification measure, and Caregiving. The caregiver outcome measure will include a score of the questionnaire evaluating caregiver’s basic nutrition and feeding knowledge before and after the intervention.

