**Data management and analysis.**

Descriptive statistics will be performed by tabulation of the summary means of the individual condition levels and baseline social demographic characteristics of the children and their caregivers. Participants’ characteristics will be presented in frequency tables. A two-way analysis of variance (ANOVA) will be performed to test the independent main effects of PD and PFT, and the effect of interaction of both PD and PFT. Factor levels will be compared by a pairwise comparison of treatment means (standard error of a difference) or a fisher’s least significant difference (LSD) test. This analysis will be done in both intention to-treat and per-protocol assumptions. All analysis will be expressed in 95% two sided confidence intervals and a p-value of <0.05 will indicate statistical significance.

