**Table 1: A 2x2 table showing the allocations of the different experimental conditions in a factorial design.**

|  | PD-Yes | PD-No |
| --- | --- | --- |
| PFT-Yes | 31 (PFT-Yes, PD-Yes) | 31(PD-No, PFT-Yes) |
| PFT-No | 31 (PFT-No, PD-Yes) | 31 (PD-No, PFT-No) |
|  | 62 | 62 |

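### The stated 80% power (malnutrition 64% vs 29%) does not apply to the trial's primary test, and 124 in total does not agree with 32 per condition

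*Protocol*

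**What the plan says.** The Protocol section on sample size estimation gives two calculations.

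- **Precision.** For a main effect in a 2x2 design it takes a 95% confidence interval of width 2.0, an error variance of 8.0 and coefficients of 0.5 and -0.5, and reaches about 31 per group.
- **Power.** It cites a report that 87% of PD participants gained at least 200 g in 12 days. It takes 64% malnourished from the 2015 assessment of the CURIE cohort and says "we hope to reduce malnutrition in the CP child population to about 29" per cent, "at α =0.05, and power (1-β) =0.8". It then states that "the estimated total sample size is 62: Hence 31 participants per each of the four arms", and concludes that "124 participants will be required for the study with 32 participants in each of the four conditions".

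Other sections bear on this:

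- **Outcome measures:** "The primary outcome measure will be a weight gain of >200grams in 12 days", joined with a gain of at least 900 g within 3 months. Z-score change and MUAC class are secondary.
- **Study population, Defining malnutrition and the flow chart:** only malnourished participants enter. The second of these says "The caregiver of a child or adolescent who is identified as MAM will be enrolled".
- **Data management and analysis:** a two-way ANOVA tests both main effects and the interaction. "All analysis will be expressed in 95% two sided confidence intervals".
- **Table 1:** 31 in each of the four cells and 62 at each PD level.

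**The concern.** A power figure has meaning only for a named outcome, a control rate and a comparison. Here all three differ from the trial's primary test:

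- the outcome is malnutrition prevalence instead of weight gain;
- the reference rate belongs to an unselected cohort instead of a malnourished sample;
- the comparison is one group of 31 against another, while a factorial main effect sets 62 against 62.

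The target of 29% is attributed to the reported PD effect. That effect is on another measure, and the protocol gives no comparator rate for it.

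At stake is how the result is read. If the primary comparison is null, nothing in the protocol tells a reader what difference the trial could have found. The two cell sizes also leave the recruitment target unclear by four participants.

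**Working it through.** **Inputs.** 64%, 29%, alpha 0.05 and power 0.80 come from the sample size section. Two-sided testing is taken from the analysis section, because the sample size section does not state it.

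**1. Reproducing the plan's figure.** Pooled two-proportion formula without continuity correction, mean proportion 0.465:

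n = [1.96 x sqrt(2 x 0.465 x 0.535) + 0.842 x sqrt(0.64 x 0.36 + 0.29 x 0.71)]² / 0.35² = (1.382 + 0.556)² / 0.1225 = 30.7

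This rounds up to 31 per group, 62 in all, as stated. The arithmetic on the stated inputs is right.

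**2. What the 80% refers to.** Power = Phi{[0.35 x sqrt(n) - 1.382] / 0.661}.

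- 31 vs 31 (one cell against another): (1.949 - 1.382) / 0.661 = 0.857, power 80.4%.
- 62 vs 62 (main effect with 31 per cell): (2.756 - 1.382) / 0.661 = 2.079, power 98.1%.

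So 62 is a two-group total. Giving 31 to each of four arms does not follow from it, and after that step 80% no longer describes a main effect.

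**3. The 64%.** If all participants are malnourished at entry, 64% still malnourished in the control condition at follow-up requires 100% - 64% = 36% of controls to recover. The protocol neither states nor justifies such a rate.

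**4. The 29%.** The only effect cited is 87% reaching a weight gain. No step from 87% to 29% malnourished is shown.

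**5. Power on the primary outcome.** The protocol gives 87% under PD for the 12-day gain and no control rate, so the control rate below is an assumption. The formula is that of step 2 with 87% against the control rate, two-sided 0.05.

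| Assumed control response | Power, 62 vs 62 | n per PD level for 80% power |
|---|---|---|
| 50% | 99.7% | 24 |
| 60% | 93.6% | 41 |
| 65% | 82.6% | 58 |
| 70% | 63.7% | 91 |
| 75% | 39.7% | 167 |
| 80% | 18.0% | 441 |

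These figures make no allowance for attrition.

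**6. Interaction, for scale.** Three cells at 64% and one at 29% give an interaction of 35 points. SE = sqrt[(3 x 0.64 x 0.36 + 0.29 x 0.71) / 31] = sqrt(0.8971 / 31) = 0.170. Power = Phi(0.35 / 0.170 - 1.96), about 54%.

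**7. The precision calculation.** The formula itself is in a figure not available here. The usual form gives 4 x 8 x (4 x 0.25) x (1.96 / 2)² = 30.7, or 31.2 with a small-sample term. Both agree with about 31 per group. The text names no outcome or unit for 8.0 and 2.0.

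**8. The total.** 4 x 31 = 124; 4 x 32 = 128. The recruitment text and flow chart use 124, and Table 1 uses 31.

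**The case against.** The strongest defence is that 31 per cell does not depend on the power paragraph. The precision calculation is set up for a factorial main effect and reaches the same number. That stands, and it is why enrolment need not change. It does not supply power for the primary outcome, however, because the text does not tie its variance and width to weight gain or to any unit. The missing figure might have done so, which limits how hard this can be pressed.

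A second defence is that the step from 62 to four arms of 31 errs on the safe side: on the plan's own inputs a main effect has 98.1%, not 80%. That is also true. A reader might infer from the mismatches that the trial is too small, but the documents do not show this.

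Three other strong readings also fail.

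- One might call 64% vs 29% impossible in a sample malnourished at entry. It is possible if 36% of controls recover. Also, the flow chart lists MUAC among the entry indicators, so a child might qualify without a Z-score below -2 in the indices behind the 64%. The rate is unjustified, not impossible.
- One might say that the protocol claims 80% power for the interaction. It does not. The only factorial effect named in the sample size section is a main effect, and the analysis section merely lists the interaction among its tests.
- One might call the cited 87% uncontrolled. The source is not at hand. All that can be said is that the protocol gives no comparator rate.

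**Conclusion.** The point holds in this form: the protocol's only power statement does not apply to its primary test. It uses another outcome, a reference rate from a different population, a target whose derivation is not shown, and a comparison of 31 with 31 where a main effect has 62 against 62. The formula was applied correctly; the fault lies in what was put into it and in how the result was carried to four arms.

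Power for the primary comparison is unknown from the document. With 87% response under PD on the 12-day criterion, it exceeds 80% if the control response is 65% or lower and falls to 64% at 70% and 18% at 80%. That range rests on the assumed control rates, on carrying the cited 87% over to this population, on the 12-day criterion alone and on complete follow-up. For parent facilitator training (PFT), which follows geographic village clusters, no such figure holds without allowing for that allocation.

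The conflict between 124 and 32 per condition is certain but minor. Since 31 appears in both calculations and in Table 1, 32 looks like a slip.

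**What to change.** Rewrite the sample size section, leaving enrolment at 124:

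1. Replace the 64% vs 29% statement with what 31 per cell, and so 62 vs 62 per main effect, delivers on the weight-gain responder outcome. State the control response as an assumption and show a range. For example, 87% under PD on the 12-day criterion against 50 / 60 / 65 / 70 / 75 / 80% gives about 99.7 / 94 / 83 / 64 / 40 / 18%. Say that this is before attrition and, for PFT, before allowing for allocation by geographic cluster.
2. State that the figure is for main effects and that no power is claimed for the interaction.
3. Give the outcome and units of the variance of 8.0 and the width of 2.0.
4. Change 32 to 31 per condition, to agree with 124 and Table 1.

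The cost is the rewording of one section. The drawback is that the stated power becomes conditional on an assumed control rate and may look less favourable than 80%.

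### The only stated power (80%) is for malnutrition status, which is not a listed outcome, so power for the primary weight-gain outcome is not established

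*Protocol*

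**What the plan says.** The Protocol's section on sample size estimation contains two calculations.

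- The first is a precision calculation for a main effect in the 2x2 factorial design: 95% confidence, interval width 2.0, within-group error variance 8.0, about 31 per group. It names no outcome or unit and states no power.
- The second compares two proportions. Its starting rate is given as: "Based on the prevalence of malnutrition (<-2sd in any of HAZ,WAZ,BMIZ) among the CURIE CP population based cohort reported as 64" per cent. Its target, error rate and power are: "we hope to reduce malnutrition in the CP child population to about 29%, at α =0.05, and power (1-β) =0.8". The result is: "the estimated total sample size is 62: Hence 31 participants per each of the four arms". The total follows: "assuming a 1:1:1:1 allocation, 124 participants will be required for the study".

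The section on outcome measures heads the primary outcome as nutritional status and then defines it: "The primary outcome measure will be a weight gain of >200grams in 12 days", together with at least 900 g within 3 months. The secondary outcomes are "change in anthropometric Z scores for any of weight, height and BMI, and MUAC classification measure, and Caregiving". The last of these is measured by a caregiver knowledge score.

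The proportion below -2 SD in any index serves as the definition of malnutrition and as the entry criterion in the flow chart. It is not listed as an outcome.

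**The concern.** The endpoint that carries the 80% and the endpoint named as primary are different events. A child can gain 900 g and still be below -2 SD. A child with height-for-age below -2 SD counts as malnourished under the sizing definition however much weight is gained in 3 months. Power for one therefore does not carry over to the other.

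The 64% has a second problem. It is the prevalence in the whole CURIE cohort, but the trial enrols only caregivers of malnourished children. It is not a justified comparator rate for this sample, even for the endpoint that was sized.

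What is at stake is how the result is read. A reader will naturally attach the 80% to the primary outcome, and could then take a null weight-gain result as evidence against PD, although power for that outcome was never worked out.

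**Working it through.** **1. Reproduce the plan's figure.** Inputs from the sample size section: p1 = 0.64, p2 = 0.29, alpha 0.05, power 0.80. That sentence does not state sidedness; the analysis section does: "All analysis will be expressed in 95% two sided confidence intervals". The pooled formula, without continuity correction, is

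n per group = [z(0.975) x sqrt(2 x pbar x (1 - pbar)) + z(0.80) x sqrt(p1(1 - p1) + p2(1 - p2))]^2 / (p1 - p2)^2

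- pbar = (0.64 + 0.29)/2 = 0.465, and sqrt(2 x 0.465 x 0.535) = 0.7054
- sqrt(0.2304 + 0.2059) = 0.6605
- n = [1.960 x 0.7054 + 0.8416 x 0.6605]^2 / 0.35^2 = 1.938^2 / 0.1225 = 30.7, so 31 per group and 62 in total

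Power at 31 v 31 is 80.4%. The stated figure reproduces, and no weight-gain rate enters it.

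**2. Does the other calculation supply power?** 4 x 8.0 x 1 x (1.96/2.0)^2 = 30.7, again about 31 per group. This fixes an interval width for an unnamed outcome. It gives no power for weight gain.

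**3. Does the 29% carry weight-gain information?** The section cites 87% of PD participants in a Burundi study gaining at least 200 g in 12 days, and offers the 29% as assuming that effect. No step links the two. Applying 87% as a cure rate gives 0.64 x (1 - 0.87) = 0.083, not 0.29. The fall actually assumed is (0.64 - 0.29)/0.64 = 55% in relative terms.

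**4. What can be said about weight gain at the existing N?** The 87% is the only weight-gain rate in the document, and no comparator rate is given. Assumptions: 87% respond in the whole PD-Yes margin, the PD-No rate is varied, children are independent and none are lost. Table 1 gives 62 PD-Yes v 62 PD-No. The power formula is

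power = Phi{[|p1 - p2| x sqrt(n) - 1.960 x sqrt(2 x pbar x (1 - pbar))] / sqrt(p1(1 - p1) + p2(1 - p2))}

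Example at a PD-No rate of 65%: pbar = 0.76, and [0.22 x 7.874 - 1.960 x 0.6040] / 0.5836 = 0.94, so power is 83%.

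| Assumed PD-No rate, 200 g in 12 days | Power, 62 v 62 |
|---|---|
| 50% | 99.7% |
| 55% | 98% |
| 60% | 94% |
| 65% | 83% |
| 70% | 64% |
| 75% | 40% |
| 80% | 18% |

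Power reaches 80% at a PD-No rate of about 66% or lower.

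**5. Limits of the table.** It covers the 200 g component only. The document gives no rate for at least 900 g within 3 months, so power for the full primary outcome cannot be calculated from it. The PD-No margin is also not an untreated group: 31 of its 62 children receive parent facilitator training (PFT). The rate that matters is the average over the PFT-only and neither-intervention cells. For instance, 60% in one and 72% in the other average 66%.

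**The case against.** The strongest reply is that the two endpoints are related. The primary outcome is headed nutritional status, Z-score change and MUAC class are secondary outcomes, and the sizing endpoint dichotomises the same kind of Z-scores. The 29% is said to rest on an effect reported as weight gain, and the precision calculation reaches about 31 per group independently. Part of this stands: the sizing endpoint is not foreign to the trial, and 124 does not rest on 64% v 29% alone. But the heading is followed by an explicit measure in grams, change in a score is not the proportion below a cut-off, the 87% is not an input to the test, and the precision calculation has no power and no named outcome.

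A second reply is that 95% confidence intervals are promised, so a null result would show its own uncertainty. That limits the harm, but it does not make the power statement apply to the primary outcome.

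A reader might infer more than the document supports:

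- **That the trial is underpowered for weight gain.** This is not shown. Power depends on an unstated PD-No rate, and at 60% or lower it is at least 94% for the 200 g component.
- **That the sample size arithmetic is wrong.** The 31 per group reproduces.
- **That using 64% flatters the power.** This does not follow. With the 29% target kept, a comparator rate of 90% would give more than 99.9% power at 31 v 31. The fault is that 64% is not justified for this sample, not that it errs in a known direction.
- **That malnutrition status will never be reported.** The protocol records anthropometry to track nutritional status, and the analysis plan is not at hand.

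**Conclusion.** The point holds as a mismatch within the protocol: the 80% belongs to malnutrition status, and the weight-gain primary outcome has no established power. This is not something left to an analysis plan, because the protocol itself fixes the power claim on one endpoint and names another as primary. Its size can be bounded only for one component: over assumed PD-No rates of 60% to 75%, power runs from about 94% down to 40%. This rests on the external 87% applying to this trial's PD-Yes margin and on the simplifications listed in the working. The point should be fixed, but it is not critical: neither the sample nor the visit schedule needs to change.

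**What to change.** Keep N at 124 and revise the sample size section as follows.

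1. State that the 80% refers to malnutrition status (below -2 SD in any of the three indices) and not to the primary outcome, and that 64% is a cohort prevalence rather than a comparator rate for a sample that is malnourished at entry.
2. Replace it as the trial's power claim with power for the weight-gain outcome on the PD main effect, 62 PD-Yes v 62 PD-No, over a stated range of assumed PD-No responder rates. Note that half of the PD-No children receive PFT.
3. If the figures tabulated in the working are used, label them as assumptions for the 200 g in 12 days component only. Printing them as power for the whole primary outcome would repeat the fault.
4. State that no rate is available for the component of at least 900 g within 3 months, so power for the full primary outcome is not established.

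Adding status below -2 SD at 3 months as a named secondary outcome is optional. If it is added, the wording must allow for children admitted on MUAC who may not be below -2 SD on the three indices at baseline.

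The cost is protocol wording and one recalculation, with no extra participants or visits. The stated power may become less favourable.

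### The sample size section sets 32 participants in each of four conditions for a total of 124, but 4 × 32 = 128; every other figure in the protocol gives 31 per condition

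*Protocol*

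**What the plan says.** The Protocol's section on sample size estimation uses two methods.

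- The first is a precision calculation for a main effect in the 2×2 design. It is reported as giving about 31 per group.
- The second compares two proportions. Malnutrition is "among the CURIE CP population based cohort reported as 64% as per the 2015 assessments", and of the intervention the protocol says "we hope to reduce malnutrition in the CP child population to about 29" per cent, "at α =0.05, and power (1-β) =0.8". The reported result is 62 in total, followed by "Hence 31 participants per each of the four arms".

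The next sentence assumes equal allocation to the four conditions and sets the target: "124 participants will be required for the study with 32 participants in each of the four conditions".

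The figures appear again elsewhere in the Protocol:

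- Under the definition of malnutrition, caregivers are enrolled consecutively "to make-up for the required study sample (124 caregivers").
- The study flow chart gives 124 for the malnourished children who are included.
- Table 1 puts 31 in all four cells, the first reading "31 (PFT-Yes, PD-Yes"), with column totals of 62 and 62.

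**The concern.** One sentence fixes both the total and the number per condition, and the two cannot both be met. Both also bear on recruitment. The section on defining malnutrition enrols until the overall total is reached. The section on randomization and blinding brings in children from other organisations to make up what each of the four conditions needs. Someone working from this sentence alone could plan for 124 or for 128.

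What is at stake is mainly the clarity of a key design number. The protocol is still to go to the ethics bodies, according to its ethical considerations section, so the number should be unambiguous in what they receive.

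**Working it through.** **1. Cell arithmetic.** 124 / 4 = 31. 4 × 31 = 124. 4 × 32 = 128. The excess is 128 − 124 = 4 participants, or 4/124 = 3.2%.

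**2. Two-proportion calculation.** Inputs from the sample size section: p₁ = 0.64, p₂ = 0.29, α = 0.05, power 0.80. That section does not state sidedness. It is taken as two-sided from the data management and analysis section: "All analysis will be expressed in 95% two sided confidence intervals and a p-value of <0.05 will indicate statistical significance". With pooled variance under the null and no continuity correction:

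n per group = [z₀.₉₇₅ √(2p̄(1−p̄)) + z₀.₈₀ √(p₁(1−p₁) + p₂(1−p₂))]² / (p₁ − p₂)², where p̄ = (0.64 + 0.29)/2 = 0.465

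= [1.960 × 0.7054 + 0.8416 × 0.6605]² / 0.35² = 30.7, rounded up to **31**

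This reproduces the protocol's 31 per arm and 62 per two-group comparison, and four cells of 31 give 124. Variants of this calculation give 25 (one-sided), 30 (one-sided with continuity correction), 28 (two-sided, unpooled) and 37 (two-sided with continuity correction). None gives 32.

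**3. Precision calculation.** Inputs from the same section: interval width 2.0, error variance 8.0, coefficients 0.5, 0.5, −0.5, −0.5, whose squares sum to 1. The formula itself is in a figure that is not shown, so its form is an assumption here:

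n per group = 4 × variance × Σc² × (z/width)² = 4 × 8.0 × 1 × (1.96/2)² = 30.7, rounded up to **31**

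This reproduces the stated figure. Adding a small-sample term z²/8 = 0.48 gives 31.2.

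**4. The stated figures side by side.**

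| Place in the Protocol | Per condition | Total |
|---|---|---|
| Sample size, precision method | about 31 | – |
| Sample size, two proportions, result sentence | 31 | 62 for two groups |
| Sample size, target sentence | **32** | 124 |
| Defining malnutrition | – | 124 |
| Study flow chart | – | 124 |
| Table 1 | 31 in each cell | 62 + 62 = 124 |

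The figure 32 occurs once. The protocol states no dropout allowance or rounding rule that would account for it, and a dropout allowance would have raised the total as well.

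**5. Effect on power.** Same inputs and same normal approximation:

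| Comparison | Group sizes | Power |
|---|---|---|
| Two cells | 31 v 31 | 80.4% |
| Two cells | 32 v 32 | 81.7% |
| Two cells, hypothetical | 32 v 28 | 78.9% |
| Main effect | 62 v 62 | 98.1% |
| Main effect | 64 v 64 | 98.4% |
| Main effect, hypothetical | 64 v 60 | 98.1% |

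The hypothetical rows take three cells filled to 32 with enrolment stopped at 124, which leaves 124 − 3 × 32 = 28 in the fourth.

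**The case against.** The strongest reply is that the protocol settles the matter itself. The total is 124 everywhere, Table 1 is the allocation table and is unambiguous, and the sentence just before the disputed one says 31. On that view this is a slip that no careful reader would act on. Much of this stands: the intended figure is very probably 31, and the overall target is not in doubt. It does not remove the error, because the sentence that states the requirement still gives a number per condition that is incompatible with its own total.

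It could also be argued that 32 was deliberate. The precision formula with the small-sample term gives 31.2, which rounds up to 32. But the protocol reports about 31 from that method, and a deliberate 32 would require a total of 128, which appears nowhere.

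A reader might infer three stronger things that the document does not support:

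- *That recruitment would end at 32/32/32/28.* No section says that cells are filled one after another and closed at 32. Participants from the existing study are randomly assigned within each of its two arms, others are placed by home village, and no filling order is set. The design is quasi-randomised, so exact balance is not guaranteed in any case.
- *That the trial would be underpowered.* Even in that split the loss is 80.4 − 78.9 = 1.5 percentage points, and only for comparisons with the short cell. Pairwise comparisons are planned, but the analysis section names the main effects of the two interventions first, and their power stays at about 98%.
- *That 128 would exceed an approved total.* The ethical considerations section says approval of this protocol is yet to be sought. The approval already obtained is for the wider intervention study. No approved number is documented.

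**Conclusion.** The statement is wrong as written. Four conditions of 32 make 128, not 124, and 32 is the only figure that disagrees with both calculations, the preceding sentence, Table 1 and the repeated total. Because it is a stated sample size, it merits correction rather than being passed over as a typing slip.

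Its size is 4 participants, or 3.2% of the total. Two-cell power differs by 1.3 points between 31 and 32 per cell (80.4% v 81.7%), and main-effect power is about 98% on either figure. No conclusion about the adequacy of the design follows from this point.

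The contradiction rests on arithmetic alone and needs no assumption. The power figures assume the protocol's 64% v 29%, a two-sided 5% test, independent participants and a normal approximation with pooled variance under the null. The main-effect figures also assume that the same contrast applies to the pooled margins.

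**What to change.** In the target sentence of the sample size section, change 32 to 31, so that it reads as 31 in each of the four conditions (4 × 31 = 124). This agrees with both calculations, Table 1, the section on defining malnutrition and the flow chart. It is a one-word correction and costs nothing.

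If 32 was in fact intended, give the reason, change the total to 128 in the sample size section, the section on defining malnutrition and the flow chart, and change Table 1 to 32 per cell with column totals of 64. That costs 4 more participants.
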